### Randomization and blinding

When the baseline questionnaires and the sleep diary are completed, the participants are randomized. Randomization is computer generated, by the webbased system (CastorEdc). Block randomization (blocks of 2 or 4) will be used to create similar distributions in the different study arms. Randomization into the two treatment groups is at patient level and will be stratified by benzodiazepine use, at least once every 2 weeks (i.e., no *versus* benzodiazepine use) at baseline and by referral type (self-referral versus referral by health care worker). Randomization will be executed centrally by a researcher/assistant who is not involved in the recruitment and inclusion of patients.

The research assistant informs the participants by phone about the result of the randomization procedure and explains the CBT-I appointment or how to collect the medication at the hospital pharmacy. The coordinating researcher and participant agree upon and document the date on which the participant will start taking/attending the study treatment.

It is not possible to blind participants or therapists to allocation; statistical analysis will be conducted by an independent statistician who will be blinded for group allocation.

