### Statistical analysis

Demographic and clinical characteristics (e.g., age, gender, medical condition, preference and type of insomnia) and primary and secondary outcomes at baseline (e.g., sleep efficiency, emotional complaints) will be presented in means (standard deviations) and numbers (percentages) depending on their distribution.

The null hypothesis states that there is a difference in mean scores on the primary outcome between the treatment groups; the alternative hypothesis is that the difference in mean scores on the primary outcome measure does not differ by more than the non-inferiority margin. The primary analysis will be conducted according to intention-to-treat, i.e., all randomized patients are included and are analyzed in their randomly assigned treatment group. Outcomes that are based on measurements at multiple time points, i.e., weeks 6 and 12, are analyzed using mixed linear models. Mixed linear models can handle the presence of missing data without the need for imputation and still provide valid estimates of treatment effects.

The primary outcome for analysis is the mean subjective insomnia severity as assessed using the ISI at week 12. To test for the difference between the two treatment groups, the primary outcome of ISI score at week 12 will be analyzed using analysis of covariance (ANCOVA) with treatment group (amitriptyline or CBT-I) as the independent variable and the baseline value as a covariate. We will check for violations of necessary assumptions of ANCOVA (normality, homogeneity of variance and random independent samples). We will calculate a one-sided 95% confidence interval around the mean difference in the primary outcome between the treatment groups to determine if the upper limit of the confidence interval will be below the non-inferiority margin of 4 points. Amitriptyline will be declared non-inferior to CBT-I if the upper bound of the 95% confidence interval does not exceed the non-inferiority margin of 4 points. If amitriptyline is shown to be non-inferior, we then will proceed to superiority hypothesis testing. For superiority testing, we will consider the two sided 95% confidence interval of the mean difference between both groups on the primary outcome as established in the ANCOVA and verify if it includes zero or not.

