The primary analysis will be conducted according to intention-to-treat, i.e., all randomized patients are included and are analyzed in their randomly assigned treatment group. We will use multiple imputations to handle missing data for outcomes that are based on the measurement at a single time point, including the primary outcome of the ISI score at week 12. We will include all baseline demographic and clinical characteristics in the imputation model. We will impute a total of five datasets and these will be pooled according to Rubin’s rule [63].

Additionally, the mean ISI score over time will be compared between the two treatment groups using linear mixed models with treatment group (amitriptyline or CBT-I) and time (6 and 12 weeks from baseline) included as fixed effects and ISI score at baseline included as covariate.

We will repeat the ANCOVA and the linear mixed models analysis of the ISI score as a per protocol analysis in which only patients who actually received their assigned treatment (in the CBT-I group attendance of at least 5 out of 7 sessions and in the AM group at least 70 out of 84 days medication) will be included.

Percentages responders until relapse at 2, 4, 6, 8, 10, and 12 months post treatment in both treatment groups will be compared using survival analyses. We will express the difference between amitriptyline and CBT-I in effect sizes and percentage responders. Treatment response is defined as ≥ 8 point reduction on ISI. A relapse is defined as a drawback of ≤ 8 points to the baseline score of the Insomnia Severity Index measured during follow-up at two subsequent measurements.

ANCOVA will be repeated on the secondary outcome measures assessed at week 12 and 12 months, adjusted for the baseline measurement and the linear mixed models will be repeated for the secondary outcomes sleep quality, fatigue, emotional complaints, physical functioning, impairment of functioning, and pain, all assessed at weeks 6 and 12 and 12 months post treatment adjusted for the baseline measurement, according to intention to treat and per protocol analyses. Bonferroni corrections will be applied to the p-values to account for multiple comparisons.

Rates of reported side effects, withdrawal, and rebound symptoms as well as the treatment evaluation items will be described.

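### Randomisation is stratified by benzodiazepine use and referral type, but the ANCOVA and mixed models omit both factors, so the reported standard error and confidence interval will be somewhat too wide if the strata are prognostic

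*Protocol article*

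**What the plan says.** Under Randomization and blinding, the article plans computer-generated allocation at patient level: "Block randomization (blocks of 2 or 4) will be used". Allocation "will be stratified by benzodiazepine use, at least once every 2 weeks" (yes or no, at baseline) and "by referral type (self-referral versus referral by health care worker"). That makes two binary factors and four strata.

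Under Statistical analysis, the covariates of each comparative model are named:

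- The primary outcome, ISI at week 12, is analysed by "analysis of covariance (ANCOVA) with treatment group (amitriptyline or CBT-I) as the independent variable and the baseline value as a covariate".
- The mixed model for ISI over time has treatment group and time (6 and 12 weeks) "included as fixed effects and ISI score at baseline included as covariate".
- The per-protocol analysis repeats these two models.
- For the other outcomes, "ANCOVA will be repeated on the secondary outcome measures assessed at week 12 and 12 months, adjusted for the baseline measurement", with mixed models adjusted in the same way.

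Neither stratification factor is named in any of these models. The list of moderators does not name them either. The imputation model is described more broadly, as containing all baseline demographic and clinical characteristics.

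**The concern.** Blocked randomisation within strata makes the arms nearly equal in benzodiazepine use and referral type, so differences between strata contribute almost nothing to chance variation in the treatment estimate. A model that leaves the strata out still counts those differences as residual noise. Its standard error then describes a less balanced design than the one actually run, and it is too large to the extent that the strata predict the outcome after baseline ISI.

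The consequences are an interval that over-covers, a test run below its nominal level, and some lost power. The superiority test is read from the same ANCOVA, and the secondary outcomes use models of the same form with a Bonferroni correction on top. The sponsor judged these two factors important enough to balance, so an analysis that ignores them does not match the design.

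**Working it through.** **Inputs from the article (Sample size; Statistical analysis).** Margin 4 ISI points, SD 4.4, one-sided 5%, power 90%, 84 per group, 13% dropout, 190 in total. The superiority test uses a two-sided 95% interval.

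**Input not in the article.** R², the share of the residual ISI variance (after baseline ISI) that the two strata explain. It is assumed here, over 0.02 to 0.10, with 0 as reference.

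**The plan's own figure.** With a true difference of zero, n per group = 2 × [4.4 × (1.645 + 1.282) / 4]² = 20.7, so 21, not 84. A margin of 2 gives 2 × [4.4 × (1.645 + 1.282) / 2]² = 82.9, so 83 (84 with the t distribution). That mismatch is a separate matter. It is relevant here only because 84 per group corresponds to an effective margin of 2, so power is shown at 2 as well as at 4. For dropout, 168 × 1.13 = 190.

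**Standard error.** The planned model reports SE = 4.4 × √(2/84) = 0.679, taking 4.4 as the residual SD. With the strata in the model, SE = 0.679 × √(1 − R²). Because of the stratified blocks, the planned estimate itself also varies with about this smaller SD. The reported SE is therefore too large by the factor 1/√(1 − R²), whatever the SD.

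**Error rates of the planned model.** One-sided, at the margin: Φ(−1.645/√(1 − R²)). Two-sided superiority: 2 × Φ(−1.960/√(1 − R²)).

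**Power at an effective margin of 2, true difference zero.** Planned: Φ((2 − 1.645 × 0.679) / (0.679 × √(1 − R²))). Adjusted: Φ(2 / (0.679 × √(1 − R²)) − 1.645).

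| Assumed R² | SE planned | SE adjusted | SE too large by | One-sided error | Two-sided error | Power planned | Power adjusted |
|---|---|---|---|---|---|---|---|
| 0 | 0.679 | 0.679 | 0% | 5.00% | 5.0% | 90.3% | 90.3% |
| 0.02 | 0.679 | 0.672 | 1.0% | 4.83% | 4.8% | 90.6% | 90.8% |
| 0.05 | 0.679 | 0.662 | 2.6% | 4.57% | 4.4% | 90.9% | 91.6% |
| 0.10 | 0.679 | 0.644 | 5.4% | 4.15% | 3.9% | 91.5% | 92.8% |

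Before rounding, the power difference at R² = 0.02 is 90.84 − 90.56 = 0.28 points; at 0.10 it is 1.30 points. The one-sided 95% bound lies 1.645 × 0.679 = 1.117 points above the estimate in the planned model. In the adjusted model it lies 1.106 points above at R² = 0.02 and 1.059 at 0.10.

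**At the stated margin of 4**, power exceeds 99.9% under either model.

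**Superiority, true difference of 2 points, R² = 0.10.** Planned: Φ((2 − 1.960 × 0.679)/0.644) = 85%. Adjusted: Φ(2/0.644 − 1.960) = 87%.

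**Check by simulation.** 168 patients, permuted blocks of 2 or 4 in four strata, 8,000 runs, assumed prevalences of 30% benzodiazepine use and 40% self-referral. At R² = 0.10 the planned ANCOVA reported a mean SE of 0.680 while its estimate varied with an SD of 0.648, and its error at the margin was 4.3%. With the strata included, the SE was 0.645 and the error 5.0%. At R² = 0 the two models gave the same results.

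**The case against.** The strongest reply is that nothing of consequence depends on this. The error is conservative, so it cannot create a false claim of non-inferiority. At the article's own margin and SD, power is above 99.9% with or without the strata. Benzodiazepine use may also be partly captured by baseline ISI, which is already in the model, so the residual R² could be small. All of that stands, and it limits the weight of the point.

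A second reply is that covariates belong in the analysis plan, which is not shown, and that the article does not call its list exhaustive. This stands only in part: the article names the covariate of each model, so a plan that followed it would leave the strata out.

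A reader might infer several stronger things that the article does not support:

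- **That the precision from stratifying is lost outright.** It is not. The balance is kept whatever the model; what is lost is its reflection in the standard error and interval.
- **That adjusting is worth a fraction 1/(1 − R²) more patients.** That ratio compares with an unstratified trial, whereas stratification has already delivered part of the gain. R² must also be the share left after baseline ISI, not the share of total week-12 variance.
- **That omitting the factor leaves benzodiazepine use during the trial unadjusted.** The stratum is baseline use, and a baseline covariate cannot adjust for use after randomisation.
- **That the strata are missing from every model.** The imputation model takes in all baseline demographic and clinical characteristics, which plausibly covers baseline benzodiazepine use. Referral type is less clearly covered.

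**Conclusion.** The mismatch between the stratified design and the stated models is real, and its effect is small and conservative. Its size rests on an assumed residual R² of 0.02 to 0.10, since the article gives no figure. Over that range the reported standard error is about 1% to 5% too large, the one-sided error is about 4.83% to 4.15%, and about 0.3 to 1.3 points of power are lost at an effective margin of 2. If the strata carry no information beyond baseline ISI, nothing is lost.

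The non-inferiority conclusion at a margin of 4 is practically unaffected. The benefit of correcting the models is accurate coverage, a superiority test at its nominal level, and better precision for the Bonferroni-corrected secondary outcomes. In the per-protocol set there is a further reason: excluding patients can disturb the balance that stratification produced, and the covariates would adjust for that. This is a worthwhile refinement, not a threat to validity.

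**What to change.** Add baseline benzodiazepine use (yes/no, as defined for stratification) and referral type as fixed effects in:

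- the primary ANCOVA, from which the superiority interval is also taken;
- the per-protocol ANCOVA;
- the mixed models;
- the corresponding secondary-outcome models.

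Name referral type explicitly in the imputation model, and confirm that baseline benzodiazepine use is among the clinical characteristics already included there.

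The cost is one sentence in the analysis plan and two degrees of freedom. Both variables are known at randomisation, so no new data are needed. The article reports 68 patients randomised and recruitment ongoing at submission, so the change could be fixed in advance of the analysis.

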## Interventions

### Medication

The treatment regime for the low dose of AM mimics current off-label practice as much as possible, i.e., a 12-week period of 10 mg AM, with the possibility of doubling the dosages by patients themselves at approximately 3 weeks, and medication stop at 12 weeks. Furthermore, participants who opt for a double dosage regime are allowed to return to a single dosage regime within the 12 week treatment. The participants in the AM group have a consultation with a neurologist at least once during treatment at approximately 6 weeks and at 12 weeks to evaluate the effect, dosage, and side-effects of treatment and guide medication stop. At the 6 weeks consultation, participants who doubled their dose to 20 mg at 3 weeks and wish to continue this double dose up to 12 weeks will receive prescription for a second badge AM as one badge AM is only sufficient for a single dose for 12 weeks. The neurologist inquires and motivates the adherence to medication during the appointment at 6 weeks after start of treatment. At the 12 weeks consultation, the neurologists motivate and guide medication stop.

### CBT-I

CBT-I consists of 6 weekly group sessions and a follow-up session at 12 weeks with a psychologist, specialized in insomnia and medical psychology. The treatment protocol is the manual of Verbeek et al. [43], and treatment elements are as follows: psycho-education, sleep hygiene, relaxation, behavior techniques such as stimulus control and sleep restriction, cognitive interventions, and relapse prevention. The degree of application of the behavioral techniques and sleep restriction is adapted to the medical condition (e.g., caution is advised with balance problems). If due to measures, for instance in the context of the COVID-19 pandemic, the group treatment cannot be offered face to face, the treatment will be offered by videoconferencing in group or individually via a secured connection. The psychologist inquires and stimulates adherence to CBT-I every session.

### Concomitant care during the trial

Subjects in the AM treatment group are advised to refrain from activities that require attention such as car driving when using AM in the first week. The use of other medication including benzodiazepines is allowed during participation in the trial. The only exception is the use of other psychopharmaceuticals. The general practitioner and the pharmacy of the patient is informed about study participation so that new prescriptions are checked for potential drug-drug interactions. Patients are instructed to refrain from using over-the-counter treatments as much as possible. We will monitor the use of both prescribed and over-the-counter sleep medication by questionnaire.

During the treatment period, all patients have access to written or online sleep hygiene advices provided by the participating hospital. In case of acute worsening of the insomnia due to a life-event or a comparable situation, other treatments might be prescribed by a medical doctor (such as benzodiazepines). This use will be monitored by self-report from the patient. Participants are instructed to report new or an increase of existing symptoms during the study to the clinician or researcher.

Adverse events will be treated and followed by the medical specialist conform usual practice. Participants who do not respond or relapse during the study or who request to end study participation will be invited to an individual follow-up session and offered further treatment outside the context of the study if required. The investigator and the treating physician in consultation with the research team can decide to withdraw a participant from the study for urgent medical reasons which are not predefined. The treatment can also be stopped at request of the patient. Those patients who choose to discontinue the treatment are offered the other treatment outside the context of the study.

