### Exclusion criteria

The study-related exclusion criteria are 1) habitual night shift worker, 2) an untreated sleep-related breathing disorder, 3) a wish to continue over-the-counter sleep aids as melatonin and medicinal cannabis, 4) the use of off-label amitriptyline for insomnia in the past year, 5) being unable to follow study instructions and fill out the study questionnaires in Dutch, 6) a known diagnosis of dementia or history of delirium and epilepsy, 7) pregnancy, lactation, or wish to become pregnant in the coming 6 months, 8) the presence of a severe psychiatric disorder (not in remission or not adequately treated), 9) current alcohol or drug abuse/addiction (benzodiazepine excluded), 10) terminal illness (life expectancy less than one year), 11) ocular hypertension/glaucoma, and 11) participation in other interventional studies. Furthermore, to prevent potential drug to drug interaction, subjects with 13) a current use of psychopharmaceuticals other than benzodiazepine such as antidepressants (selective serotonin reuptake inhibitors , tricyclic antidepressants, MAO-inhibitors), St John’s worth, anticonvulsants (e.g., carbamazepine), and antimyotics are excluded. Finally, subjects who are known with 14) any of the following contra-indications for amitriptyline conform pharmacological guidelines as used in clinical practice will be excluded: an allergy for amitriptyline, cardiovascular diseases (cardiac arrhythmia/blockade/long QT syndrome/Brugada syndrome, family history of acute cardiac death, recent myocardial infarction (within the past 90 days), and angina pectoris/coronary insufficiency), severe renal insufficiency (GFR < 10) or severe liver dysfunction. The exclusion criteria are based on guidelines of higher dosage amitriptyline. They are lined up to prevent, e.g., the risk of cardiac dysrhythmias, withdrawal symptoms in the newborn, and suicidal risk. Patients with dementia, severe psychiatric disorders (including suicidal risk), and patients who are not able to follow study instructions are excluded for the study, to prevent the risk of overdoses.

Table 1 summarizes the inclusion and exclusion criteria.

**Table 1 Tab1:** Inclusion and exclusion criteria

Inclusion criteria	Exclusion criteria

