18–85 years Insomnia disorder conform DSM-5 Score of ≥ 10 on the Insomnia Severity Index Long term medical condition	*Study-related exclusion criteria:* Habitual night shifts Untreated sleep-related breathing disorder Wish to continue over-the-counter sleep aids Off-label amitriptyline for insomnia in past year Epilepsy, dementia, history of delirium Pregnancy, lactation or pregnancy wish Terminal illness Ocular hypertension/glaucoma Severe psychiatric disorder Substance abuse/addiction (benzodiazepine excluded)
	*Potential drug-drug interactions for amitriptyline:* Use of psychopharmaceuticals (other than benzodiazepine) or antimyotics
	*Contra-indications for amitriptyline:* Allergy for amitriptyline Cardiac disorders Severe renal insufficiency or liver dysfunction

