## Discussion

This study protocol, which adheres to SPIRIT 2013 [64], describes the first randomized controlled trial evaluating whether AM is non-inferior to first choice treatment for insomnia CBT-I in treating insomnia in patients with medical conditions. The results will offer valuable data about the efficacy of treatments for insomnia in patients with a chronic medical condition.

This study has some limitations. First, neither the practitioner nor the participants can be blinded to allocation. Second, patients with strong preferences for one of the treatments (e.g., AM or CBT-I) may be less willing to participate in the study as randomization can allocate them to the non-preferred treatment. Therefore, we will assess treatment preference and explore its effect on the primary and secondary outcomes. Furthermore, we will assess drop out after randomization. Third, due to the potential drug-drug interactions for amitriptyline, patients using psychopharmaceuticals (other than benzodiazepines) are excluded from the study. The use of psychopharmaceuticals can be related to more severe disease burden. This might result in an underrepresentation of patients with severe disease burden. Fourth, in the present study, we focus on the non-inferiority of both treatments. If shown to been non-inferior, future research should include a cost analysis to compare the economic impact of both treatments

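### Antimyotics are barred at entry to prevent interaction with amitriptyline, but the on-study rule bars only other psychopharmaceuticals and leaves antimyotics to the check on new prescriptions

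*Protocol article*

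**What the plan says.** **At entry.** Exclusion 13 (Protocol article, Exclusion criteria) has the stated purpose of preventing drug interactions. It covers current use of psychopharmaceuticals other than benzodiazepine, gives examples, and ends: "anticonvulsants (e.g., carbamazepine), and antimyotics are excluded". Table 1 repeats the criterion under its entry on interactions with amitriptyline: "Use of psychopharmaceuticals (other than benzodiazepine) or antimyotics".

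**On study.** The section Concomitant care during the trial gives a general permission: "The use of other medication including benzodiazepines is allowed during participation in the trial". It then limits that permission: "The only exception is the use of other psychopharmaceuticals". The next sentence adds a safeguard: the general practitioner and the patient's pharmacy are told of the participation so that "new prescriptions are checked for potential drug-drug interactions". The same section also says: "Participants are instructed to report new or an increase of existing symptoms during the study to the clinician or researcher".

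**In the Discussion.** The limitations paragraph restates the interaction exclusion without mentioning antimyotics: "due to the potential drug-drug interactions for amitriptyline, patients using psychopharmaceuticals (other than benzodiazepines) are excluded from the study".

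(I keep the article's term, antimyotics. It presumably means antimycotics, that is, antifungal drugs; nothing below depends on this.)

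**The concern.** The interaction that exclusion 13 guards against can arise only while amitriptyline is being taken. The on-study rule is therefore where the restriction has to work, and the entry criterion is only its starting point. If the two rules name different drug classes, a prescriber or study physician who consults the concomitant-care section gets a different answer from one who consults the exclusion list.

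What is at stake is consistency with the trial's own safety standard. Participants have long-term medical conditions, so new medication during 12 weeks is plausible. No estimate, test or error rate depends on the point.

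**Working it through.** The plan gives no figure to reproduce here. The check is a comparison of texts plus a statement of scope.

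**1. The classes, side by side**

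| Place | Psychopharmaceuticals other than benzodiazepine | Antimyotics |
|---|---|---|
| Exclusion criteria, item 13 | barred | barred |
| Table 1 | barred | barred |
| Concomitant care during the trial | barred | not named |
| Discussion, limitations | stated as excluded | not named |

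Table 1 has 2 interaction classes; the on-study exception names 1 of them.

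**2. Could antimyotics fall under the on-study words?** In the running text of exclusion 13 they close a list that begins with psychopharmaceuticals, so one might read them as an example of that class. Table 1 speaks against this: it joins the two with *or*, as alternatives. On the article's own classification, an antimyotic is not a psychopharmaceutical.

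**3. Is the on-study rule open or closed?** It is closed. It permits other medication in general and then states that there is a single exception. A class outside that exception falls under the permission. The article is therefore not silent on the matter in a way that the full protocol would be expected to fill; it states a rule that differs from its own entry criterion.

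**4. What still applies to an antimyotic started on study?** The interaction check on new prescriptions. This is a check and not a prohibition, and the section does not say what follows if an interaction is found. The plan itself does not treat the check as a substitute for a bar: psychopharmaceuticals are subject to the same check and are barred outright as well.

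**5. Scope**

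- Patients: 190 planned, allocated 1:1, so 190/2 = 95 in the amitriptyline arm.
- Exposure: 12 weeks × 7 = 84 days of amitriptyline.
- Reach of the on-study rule as worded: the whole of participation, which the Methods/design section puts at 15 months from randomization (12 weeks of treatment plus 12 months).

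These figures say where the mismatch could matter. They do not measure how often it would. The documents give no rate of new antimyotic use, and none is assumed.

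**The case against.** The strongest reply is that the concomitant-care section should be read as a whole. It permits other medication, bars psychopharmaceuticals, and has new prescriptions screened for interactions; the screen covers every prescribed class, antimyotics included. A flat bar at entry followed by screening of new prescriptions can be a coherent design, and nothing in the documents requires the two lists to be identical. There are further safeguards: patients report new or worsening symptoms, amitriptyline patients see a neurologist at about 6 and 12 weeks, and a participant can be withdrawn for urgent medical reasons. The Discussion uses the single word psychopharmaceuticals for the interaction exclusion although antimyotics plainly remain excluded, so shorthand is a credible explanation. The article also condenses a fuller protocol (version 4.3), which may hold a detailed list.

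Much of this stands. The safeguards lower the practical risk, and the wording may well be shorthand. It does not remove the point. The Discussion sentence concerns generalizability and claims no complete list; the concomitant-care sentence is the operative rule and does claim one. If the full protocol has the right list, the article reports it wrongly.

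Two stronger readings are tempting and not supported:

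- *That patients are exposed to a dangerous combination.* The Exclusion criteria section says that the criteria derive from guidelines for higher-dose amitriptyline. Whether the interaction matters clinically at 10 to 20 mg cannot be judged from the documents.
- *That antimyotics bought without prescription escape all control.* The section does say "Patients are instructed to refrain from using over-the-counter treatments as much as possible", which discourages and does not prohibit. But the documents do not say that any antimyotic covered by exclusion 13 is sold without prescription, or that such a product would interact at this dose. That argument needs outside knowledge and forms no part of the point.

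**Conclusion.** The point holds as a minor inconsistency in a safety rule. Exclusion 13 and Table 1 bar two classes because of interaction with amitriptyline; the on-study rule bars one and says that it is the only one. Taken literally, an antimyotic started during amitriptyline treatment is not prohibited and is subject only to the prescription check.

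The size is small: one drug class, one arm of 95 planned patients, 84 days. The number of patients affected cannot be estimated. Sample size, power and the primary analysis do not change. The conclusion assumes that the article's sentence is meant as the operative rule and that Table 1's separation of the two classes is deliberate. If the sentence is shorthand, the plan is sound and only its wording needs correcting.

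**What to change.** Replace the exception sentence in Concomitant care during the trial with wording such as: *The only exceptions are other psychopharmaceuticals and, in the AM group while amitriptyline is being taken, the antimyotics barred by exclusion 13. A patient who needs one stops amitriptyline but remains in follow-up and in the intention-to-treat analysis.* No antimyotic restriction is needed in the CBT-I arm or after amitriptyline has stopped. The list of agents can stay in the full protocol. Should the sponsor consider antimyotics acceptable at 10 to 20 mg, the alternative is to amend exclusion 13 and Table 1, so that entry and on-study rules still agree.

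The cost is one sentence and slightly more restriction on concomitant medication in the amitriptyline arm for 12 weeks. A patient who stops with fewer than 70 of the 84 medication days leaves the per-protocol set under the existing definition; the intention-to-treat set is unchanged. At submission 68 of 190 had been randomized, so at that stage the correction could still have covered 190 − 68 = 122 planned participants.
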